### 3.6. Data Collection

The data for each study participant will be incorporated into the electronic Case Report Form (eCRF) using REDCap [22] designed specifically for this purpose. The data recorded in the eCRF will be directly imported from the computerized medical records.

### 3.7. Data Variables

#### 3.7.1. Primary Dependents Variables

Positive NECPAL identification.Mortality at 3, 17, and 38 months.

#### 3.7.2. Independent Variables

NECPAL instrument: SQ (+/−) and number of positive parameters.The patient receives PC (Yes/No).Quality of Life: assessed using the EuroQol 5D-5L questionnaire.Demographics: age, gender.Chronic conditions: cancer and non-oncological advanced chronic conditions.Setting: outpatients and hospitalized patients.Functional status: Barthel Index scoreHealth variables: primary healthcare center visits, home visits by primary care, hospital emergency visits, number of active specialist consultations, number of daily medications consumed.Nutritional variables: albumin, lymphocytes, prealbumin, retinol-binding protein, transferrin, cholesterol, body mass index (BMI), dietary intake record.

## 4. Study Procedures

The study is being conducted at Hospital Universitario Infanta Leonor-Virgen de la Torre, a secondary-level hospital in Madrid, Spain, involving outpatients and inpatients. Eligible participants are adults aged 18 years or older with at least one advanced chronic condition or cancer, identified by physicians through electronic medical records. Advanced chronic conditions are defined, according to the criteria established by SECPAL guidelines (Table 2). Cancer describes neoplasms that cannot be cured. Physicians apply the NECPAL tool to each case, beginning with the SQ, which asks, “Would you be surprised if this patient were to die in the next 12 months?”. If the healthcare professional answers “no” to this question, the patient is considered SQ+. To be considered NECPAL+, an SQ+ patient must also meet at least one parameter from the NECPAL tool. If the professional answers “yes” to the SQ (SQ−), or if an SQ+ patient does not meet any additional NECPAL parameters, the patient is classified as NECPAL−. All patients classified as NECPAL+ are deemed to need PC. It is recorded whether the NECPAL+ patient is receiving PC or not. Mortality status (alive or deceased) is assessed and recorded at 3 (NECPAL stage I), 17 (NECPAL stage II), and 38 months (NECPAL stage III), including the date and cause of death, if applicable. Mortality data are collected through telephone follow-ups and chart reviews. The quality of life of the study population is assessed using the EuroQol-5D-5L instrument (EuroQol Research Foundation, Rotterdam, The Netherlands). The questionnaire is administered at inclusion, 3 (NECPAL stage I), 17 (NECPAL stage II), and 38 months (NECPAL stage III), if applicable. Quality of life is compared among NECPAL+ patients receiving PC, those not receiving it, and NECPAL− patients. No assessments beyond those required for usual care are conducted.

Although the study protocol does not include scheduled re-assessments of NECPAL- patients during follow-up, these individuals will continue to receive routine clinical care within the healthcare system. Any significant changes in their clinical status may prompt re-evaluation by the attending medical team, including the potential re-application of the NECPAL tool if deemed appropriate. While these additional assessments are not captured prospectively in the study database, they reflect the clinical reality and the dynamic nature of patients’ needs over time. This approach ensures that patients who may not initially meet criteria for early palliative care are not excluded from appropriate care if their condition evolves.

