### 2.2. Secondary Objectives

a.To describe in this population the functional and nutritional deterioration, the prevalent advanced chronic diseases, the demand and need for PC by the patient, their family, and the professional.b.To compare the perceived quality of life among NECPAL+ patients receiving PC, those not receiving it, and NECPAL- patients using the EuroQol 5D tool (EQ-5D).

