### 3.5. Principal Outcome Measures

Predictive accuracy of NECPAL version 4.0 (2021) tool for identifying patients who need PC.Mortality prediction accuracy at 3, 17, and 38 months.Quality of life.

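### Quality-of-life groups are compared up to 38 months, but later starts of palliative care and later changes in NECPAL status are not clearly captured, and the contrast is open to confounding by severity and to survivor selection

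*Protocol article*

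**What the plan says.** Objective b in Section 2.2 is "To compare the perceived quality of life among NECPAL+ patients receiving PC, those not receiving it, and NECPAL- patients using the EuroQol 5D tool". Section 4 repeats the comparison ("Quality of life is compared among NECPAL+ patients receiving PC, those not receiving it", with NECPAL− patients third) and schedules the questionnaire at inclusion and at 3, 17 and 38 months where applicable.

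On palliative care, Section 4 says "It is recorded whether the NECPAL+ patient is receiving PC or not". Section 3.7.2 lists the field as "The patient receives PC (Yes/No", without limiting it to NECPAL+ patients. Neither place gives a start date or a later update.

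Section 4 also says that NECPAL− patients are not re-assessed on schedule, may have the tool re-applied in usual care, and are not shut out of appropriate care if they change. It adds that "these additional assessments are not captured prospectively in the study database".

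Section 3.4 describes balancing on age, gender, chronic condition and NECPAL result. Section 5.2 names methods for mortality and survival only.

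Quality of life has three ranks: secondary in Section 2.2, principal in Section 3.5 ("Mortality prediction accuracy at 3, 17, and 38 months.Quality of life"), and an independent variable in Section 3.7.2. It is absent from the dependent variables in Section 3.7.1.

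**The concern.** Three separate mechanisms affect the comparison.

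- **Exposure after inclusion.** A NECPAL+ patient who starts palliative care at month 6 may still count as not receiving it at month 17. A NECPAL− patient may by then be NECPAL+ or receiving palliative care. No analysis plan can repair this if the dates were never recorded.
- **Confounding by severity.** Palliative care arises in usual care in a non-randomized cohort. The stated balancing does not involve palliative care receipt, prognostic stage or EQ-5D at inclusion.
- **Survivor selection.** EQ-5D at 17 and 38 months exists only for those still alive, and the tool is built to separate patients by survival.

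The Introduction says that earlier palliative care improves quality of life, so readers may well take the contrast as an effect of palliative care. A raw difference in either direction could come from case mix, deaths or outdated group membership.

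**Working it through.** **The plan's own figure.** The only sample size is for one proportion: 1.96² × 0.5 × 0.5 / 0.05² = 384.2, against 384 stated. Adding 10% gives 384 × 1.10 = 422.4 (423), or 384 / 0.90 = 426.7 (427), against approximately 420. It reproduces, but says nothing about the quality-of-life contrast.

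**Survivors.** The inputs are the survival estimates in the Introduction: 38, 17.2 and 3.6 months for Stages I, II and III. (Section 4 attaches the stage labels to the visit months in the reverse order; the Introduction's order is used here.) The article does not say whether these are medians, so that is an assumption, as is exponential survival. Then S(t) = 0.5^(t/median):

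| Stage | 3 months | 17 months | 38 months |
|---|---|---|---|
| I | 0.5^(3/38) = 95% | 0.5^(17/38) = 73% | 0.5^(38/38) = 50% |
| II | 0.5^(3/17.2) = 89% | 0.5^(17/17.2) = 50% | 0.5^(38/17.2) = 22% |
| III | 0.5^(3/3.6) = 56% | 0.5^(17/3.6) = 4% | 0.5^(38/3.6) = 0.1% |

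If the figures are means instead, S(t) = exp(−t/mean) gives 64%, 37% and 1% at 17 months. Under a hypothetical equal stage mix and the median reading, Stage III falls from 33% of NECPAL+ patients at inclusion to 23% of survivors at 3 months, 3% at 17 and 0.1% at 38.

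**Case mix alone (hypothetical).** Assume no effect of palliative care and mean EQ-5D of 0.65, 0.50 and 0.35 in Stages I, II and III. Let the stage mix be 20/40/40% with palliative care and 40/40/20% without.

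- At inclusion: (0.2×0.65 + 0.4×0.50 + 0.4×0.35) − (0.4×0.65 + 0.4×0.50 + 0.2×0.35) = 0.47 − 0.53 = −0.060.
- Weighting each stage by its survival, the difference becomes −0.054 at 3 months, −0.031 at 17 and −0.024 at 38.
- With a stronger imbalance (10/30/60% against 50/35/15%) the four values are −0.128, −0.119, −0.068 and −0.051.

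So a difference can appear with no effect, and can drift through deaths alone. The negative sign follows from the assumed mix. Reversing the mix reverses the sign.

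**Outdated group membership (hypothetical).** Suppose a fraction q of the group recorded as not receiving palliative care has started it, and takes on the full difference D. The observed contrast is D − qD = (1 − q)D. For q of 10%, 20%, 30% and 40%, it keeps 90%, 80%, 70% and 60% of D.

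The article gives no palliative care uptake, no rate of later starts and no EQ-5D means, so none of these illustrations estimates the bias in this study.

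**The case against.** The strongest reply is that this is a condensed article about an openly observational cohort. The objective says compare and claims no effect, and covariates and the handling of death belong in an analysis plan that is not shown. Much of that stands, and it rules out several stronger readings that a reader might infer.

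- **That EQ-5D at inclusion goes unused.** It is collected, and Section 5.2 names no quality-of-life analysis at all. Silence is not a decision to leave it out.
- **That palliative care is recorded only in NECPAL+ patients.** Section 4 reads that way, but Section 3.7.2 has no such limit. This is a conflict to reconcile, not a settled fact.
- **That patients select their own group.** Physicians assign NECPAL status, and palliative care arises in usual care.
- **That recipients are sicker, so the bias runs against palliative care.** This is plausible, but nothing in the article shows it.
- **That the late comparisons mean nothing.** The survival figures are by stage, while the contrast is by palliative care and NECPAL status. Differential selection also needs stage to be unevenly spread across those groups. Section 3.3.2 excludes a projected life expectancy under 3 months, so Stage III survival here may differ from the tool's figure. In the illustration the spurious difference shrinks with time.

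It is also fair to say that NECPAL status at inclusion does not become wrong when a patient later changes, and that the comparison at inclusion is unaffected. The data-capture point survives all of this, because an analysis plan cannot supply dates that were not recorded. So do the conflict between Sections 3.7.2 and 4 and the three ranks of quality of life.

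**Conclusion.** The point holds in this form and should be corrected; the mortality objective does not depend on it. As described, the plan does not capture the start of palliative care after inclusion or re-application of NECPAL in NECPAL− patients, so the 3-, 17- and 38-month groups can become mixed with no means of correction in the study database. A raw contrast by palliative care is also open to confounding by severity.

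The late contrasts are among survivors: about 73%, 50% and 4% of Stages I, II and III at 17 months if the tool's figures are exponential medians, or 64%, 37% and 1% if they are means. Either way Stage III nearly disappears. The size and direction of the resulting bias are unknown, because they depend on palliative care uptake by stage, which is not given.

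Separately, visits at 17 and 38 months need reconciling with the 12-month follow-up per patient in Section 3.2.

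**What to change.** 1. Reconcile Sections 3.7.2 and 4 on who has palliative care recorded. At the chart reviews already planned for mortality, record for all patients the palliative care status and start date, and any NECPAL re-application with its date and result.
2. Within NECPAL+, compare follow-up EQ-5D by palliative care status with adjustment for data already collected: EQ-5D at inclusion, stage, Barthel Index, cancer or non-cancer, setting and age. In patients already receiving palliative care at inclusion, that first score was taken after exposure began, and adjusting for it may remove part of the association. Show results with and without that term.
3. Report EQ-5D at 17 and 38 months beside the proportion alive in each group. Keep the NECPAL− comparison of objective 2.2b, stated as unadjusted and non-causal, and word all conclusions as association.
4. Give quality of life one rank across Sections 2.2, 3.5 and 3.7.

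The cost is a few eCRF fields, a little extra chart abstraction, some text edits and a narrower quality-of-life claim. It is best done now: Section 3.4 reports 105 patients included against a target of about 420, so 105 / 420 = 25% were enrolled at the time of writing. Dates for the remainder can be collected as they occur.

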## 5. Statistical Analysis

### 5.1. Sample Size Calculation

To determine the appropriate sample size for our study, we considered a population of approximately 350,000 inhabitants. Employing a 95% confidence level (Z = 1.96), a 5% margin of error (E = 0.05), and assuming maximum variability (*p* = 0.5), the initial sample size was calculated to be 384 participants. We applied a 10% oversampling rate to account for potential non-responses, increasing the target sample size to approximately 420 participants.

### 5.2. Analysis

Quantitative variables will be expressed as means with standard deviations, and categorical variables as absolute frequencies and percentages. To evaluate the association between NECPAL+/– and mortality at 3, 17, and 38 months, we will analyze sensitivity, specificity, positive predictive value (PPV), and negative predictive value (NPV). Mortality rates will be compared using the chi-square test for equality of proportions. The Kaplan–Meier method will be used to estimate non-parametric survival curves, and the log-rank test will be applied to assess their differences. Additionally, a semi-parametric Cox proportional hazards regression model will be performed to predict the risk of death. Statistical analyses will be performed using the Statistical Package for Social Science version 29.0 (SPSS Inc., Chicago, IL, USA). A value of *p* < 0.05 will be defined as statistically significant.

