## Abstract

Early initiation of palliative care in patients with advanced chronic conditions significantly improves their quality of care; however, variability in disease trajectories complicates such interventions’ timing. The NECPAL CCOMS-ICO prognostic tool was developed as a straightforward instrument to help healthcare providers in all clinical settings promptly identify patients with advanced chronic conditions who require palliative care, thereby enhancing service planning and delivery. Its latest version, 4.0, 2021, for the first time, incorporates a patient survival estimation. Nevertheless, validation is necessary. This study aims to validate the NECPAL version 4.0 tool in an independent cohort. It is an observational, prospective study involving outpatients and hospitalized non-randomized patients at Hospital Universitario Infanta Leonor–Virgen de la Torre in Madrid, Spain, all of whom have at least one advanced chronic condition. The study is scheduled to last 6 years, including a recruitment period of 30 months starting 1 February 2024, followed by a 12-month follow-up period for each patient. This is the first prospective study designed to validate the NECPAL version 4.0 instrument. Implementing this tool would allow the identification of patients with advanced chronic conditions and unmet palliative care needs and determine the more appropriate care pathway at the proper moment.

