As the early identification of patients in need of PC could meet patients’ treatment goals and improve their quality of life, it is imperative to screen these patients using a highly accurate screening tool. The NECPAL CCOMS-ICO tool, developed by the Catalan Institute of Oncology in Spain, aims to identify early patients with advanced chronic conditions requiring PC across the healthcare system [16]. This instrument can be used in outpatient and in-hospital environments. It combines a simple SQ, ‘Would you be surprised if this patient died within the next 12 months?’, with six parameters. The parameters of the NECPAL instrument include (1) Palliative Needs Identified, where healthcare professionals determine if the patient requires PC; (2) Functional Decline, assessing the patient’s ability to perform daily activities; (3) Nutritional Decline; (4) Multi-Morbidity, indicating the presence of more than two chronic diseases added to the principal condition; (5) Use of Resources, relating to the frequency of emergency admissions or increased demand for medical interventions within six months; and (6) Specific Disease Criteria, which assesses the severity or progression of the specific chronic conditions. A patient is NECPAL+ if the SQ is answered positively (SQ+) and at least one parameter is met. Its latest version, 4.0, 2021, for the first time, incorporates a patient survival estimation (Supplementary Materials). NECPAL+ patients are categorized into three prognostic stages to estimate survival: Stage I (SQ+ and 1–2 parameters), with an estimated survival of 38 months; Stage II (SQ+ and 3–4 parameters), with 17.2 months; and Stage III (SQ+ and 5–6 parameters), with 3.6 months (Supplementary Material S1) [17]. Incorporating mortality and prognosis assessments into the tool could more accurately pinpoint the optimal time to initiate PC. However, external validation is essential to improve their clinical performance.

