## 7. Discussion

Identifying patients likely to have unmet PC needs is crucial to ensuring they receive the appropriate care at the right time. This identification process should not only lead to a referral to specialist PC services but also guarantee a comprehensive and holistic assessment of patients. This comprehensive assessment is central to improving policy-making, service planning, and care delivery, and we must address all aspects of patient care.

The ability of current screening tools to identify patients with advanced progressive diseases who are likely to have PC needs in primary care is limited. In a systematic review, the performance metrics for the screening tools were generally poor [15]. Further research is required to identify standardized screening processes. This research, based on predicting mortality and deterioration, anticipating the PC needs, and predicting the rate and course of functional decline, would prompt a comprehensive assessment. This assessment is not just important but crucial to identify and meet their needs on time.

The identification process of these patients should not be based solely on predicting mortality, but it should also focus on anticipating their needs whenever they occur and predicting the rate and course of functional decline in order to make a proactive PC plan. Our study seeks to explore the potential of the NECPAL version 4.0 (2021) tool in our area of care. The unique feature of NECPAL, which allows for the simultaneous establishment of the appropriateness of PC and the prognosis prediction, could significantly improve patient care. Previous studies have evaluated the instrument in predicting mortality using a short cut-off (12 months), showing a moderate capacity [23,24]. To our knowledge, this study is the first to analyze the predictive capacity of the latest version of the tool that incorporates long-term mortality, offering a more comprehensive understanding of patient needs and providing a solid foundation for future research. The potential impact of our findings could inspire a new wave of research and innovation in the field of PC.

NECPAL is a straightforward instrument based on variables commonly obtained in daily practice, making it easy to incorporate into healthcare systems. The mortality prediction into risk groups could allow classified patients to undergo the three transitions. However, research is needed to evaluate predictive ability and transportability.

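### The only accuracy measures named use the pooled NECPAL+/- result, so they cannot show whether the three-stage survival estimate new to version 4.0 is right

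*Protocol article*

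**What the plan says.** The Abstract gives the purpose: "This study aims to validate the NECPAL version 4.0 tool in an independent cohort". It describes the new feature and the gap together: version 4.0, "for the first time, incorporates a patient survival estimation. Nevertheless, validation is necessary". The Introduction explains the feature: "NECPAL+ patients are categorized into three prognostic stages to estimate survival". Stage I (1–2 parameters) carries 38 months, Stage II (3–4) 17.2 months and Stage III (5–6) 3.6 months.

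Primary objective (b) in Section 2.1 is the accuracy of the instrument in predicting mortality. Section 5.2 names the accuracy analysis: "To evaluate the association between NECPAL+/– and mortality at 3, 17, and 38 months, we will analyze sensitivity, specificity", plus PPV and NPV. It then plans a chi-square comparison of mortality rates, Kaplan-Meier curves with a log-rank test, and "a semi-parametric Cox proportional hazards regression model will be performed to predict the risk of death". It names no grouping for the curves and no covariates for the Cox model.

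Section 3.7.2 lists the surprise question result and the number of positive parameters among the variables, and Section 4 records the date of death. Stage and survival time can therefore both be derived.

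**The concern.** A validation should test what the tool predicts. What version 4.0 adds is a graded prediction with a survival figure for each stage. The accuracy analysis uses those figures, rounded down to 3, 17 and 38 months, as its time points, but applies them to a yes/no result that merges the stages. Nothing in the article compares observed with stated survival in any stage.

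At stake is the answer to primary objective (b). The sensitivity, specificity, PPV and NPV of NECPAL+/- would be the same whether the stages rank patients correctly, in reverse, or not at all. A reader who took them as evidence for the version 4.0 survival estimate would be misled, and large errors in a stage's figure could go unseen.

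**Working it through.** **Step 1. What the four measures depend on.** At a horizon t, let d be the deaths and n the patients in each group.

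- Sensitivity = (d_I + d_II + d_III) / (d_I + d_II + d_III + d_neg)
- PPV = (d_I + d_II + d_III) / (n_I + n_II + n_III)
- Specificity and NPV use the survivors in the same two groups.

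Stage enters only through sums over I, II and III. Moving labels between NECPAL+ patients leaves each sum unchanged, so all four measures stay the same. This needs no assumption.

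**Step 2. What pooling hides.** Inputs: stage survival of 38, 17.2 and 3.6 months (Introduction). Assumptions not in the documents: the figures are medians, survival is exponential, and the stage mix is as shown. Mortality by t is 1 − 0.5^(t/median). For Stage II at 12 months: 1 − 0.5^(12/17.2) = 0.383.

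| Months | Stage I | Stage II | Stage III | Pooled, mix 45/45/10 | Pooled, equal shares |
|---|---|---|---|---|---|
| 3 | 5% | 11% | 44% | 12% | 20% |
| 12 | 20% | 38% | 90% | 35% | 49% |
| 17 | 27% | 50% | 96% | 44% | 58% |
| 38 | 50% | 78% | 99.9% | 68% | 76% |

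Pooled at 12 months, 45/45/10: 0.45 × 0.197 + 0.45 × 0.383 + 0.10 × 0.901 = 0.351. Equal shares: (0.197 + 0.383 + 0.901)/3 = 0.494. The pooled figure is the PPV.

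Range check: if the stage figures are means, 12-month mortality becomes 27%, 50% and 96%. The values change but the spread across stages remains.

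**Step 3. Reversed staging.** With equal shares, swap the survival of Stages I and III. Pooled mortality at 3, 12, 17 and 38 months stays at 20.2%, 49.4%, 57.5% and 76.1%. NECPAL− patients are untouched, so sensitivity, specificity, PPV and NPV do not move either, although the staging is now the wrong way round.

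**Step 4. What the other planned methods could add.**

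- Kaplan-Meier and log-rank by stage would show whether the curves differ. The log-rank test has no reference to 38, 17.2 or 3.6 months.
- A Cox model with stage as covariate would show whether the grouping separates risk. It would not check the stated survival times.
- Kaplan-Meier estimates per stage, set beside the stated figures, would make that check. The article does not mention it.

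**Step 5. Conditions on any stage-level check.**

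- Follow-up: the Abstract and Section 3.2 give 12 months per patient. Under the Step 2 assumptions, Stages I and II reach only 20% and 38% mortality by then, so neither median would be observed.
- Labels: Section 4 ties 3 months to Stage I and 38 months to Stage III. The Introduction has them the other way round.
- Selection: Section 3.3.2 excludes patients with projected life expectancy under 3 months, which bears most on Stage III.
- Precision: if Stage III were 10% of NECPAL+ patients, it would hold at most 0.10 × 420 = 42 patients. Around 50%, the 95% half-width is 1.96 × √(0.25/42) = 0.15, or ±15 points.

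**The case against.** NECPAL+/- governs one sentence of Section 5.2. The same paragraph plans Kaplan-Meier, log-rank and Cox analyses, and the number of positive parameters is collected as its own variable. Analyses by stage are therefore open, and a condensed article may leave grouping and covariates to the full protocol or analysis plan. That stands. A reader might infer that the study cannot validate the staging at all, or that the Cox model would only derive a new predictor. The documents support neither, because grouping and covariates are not named.

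It does not remove the point. The article names the classifier for its accuracy measures, and it is one that cannot speak to the staging. None of the unassigned methods, as described, is set against the stated survival times.

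A reader might also infer that leaving out 12 months is an error, since the surprise question uses that horizon. The documents do not support that. Sections 3.1, 3.5, 3.7.1, 4 and 5.2 consistently give 3, 17 and 38 months, and the Discussion presents longer horizons as the contribution: "Previous studies have evaluated the instrument in predicting mortality using a short cut-off (12 months"). Dates of death are recorded, so a 12-month figure remains obtainable. It would be a useful addition, nothing more.

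Finally, the primary objectives do not mention stages. That is true of Section 2.1. The Abstract nevertheless says that version 4.0 is being validated, and it presents the survival estimate as the feature that makes validation necessary.

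**Conclusion.** The point holds in this form: every accuracy measure that Section 5.2 names uses the pooled binary result, at horizons taken from the individual stages, so none can show whether the three-stage survival estimate is right. This follows from the definitions of the measures and rests on no assumption. It affects primary objective (b) and the study's stated purpose.

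The mortality percentages are illustrative only. They rest on exponential survival, on reading the stage figures as medians (the article calls them estimated survival), and on an assumed stage mix. Pooled mortality at 3, 12 and 17 months moves from about 12/35/44% to 20/49/58% between the two mixes.

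The plan does not rule out an analysis by stage. It fails to commit to one, and states no comparison with 38, 17.2 and 3.6 months.

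**What to change.** For objective (b), name stage (NECPAL−, I, II, III) as the analysis variable in Section 5.2 and specify:

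1. Kaplan-Meier survival per stage with 95% confidence intervals, set against 38, 17.2 and 3.6 months. First confirm from the source of version 4.0 whether these are medians.
2. Discrimination of the ordered stages by Harrell's C or time-dependent AUC, using the published staging without refitting.
3. The binary NECPAL+/- accuracy as now planned, with 12 months added at low cost. That is the horizon of the surprise question and of the earlier evaluations cited in the Discussion.

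Three matters go with this. Reconcile the 12-month follow-up per patient with the 17- and 38-month outcomes, since the Stage I and II comparisons depend on it. Reconcile the stage labels in Section 4 with the Introduction. State that the Stage III comparison will be read in light of the life-expectancy exclusion and of a possibly small group.

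The change to the analysis is one of wording. The number of positive parameters and the dates of death are already collected, so no new data items are needed. Only 105 of about 420 patients had been included when the article was written. Resolving the follow-up may cost more if patients are in fact to be followed for only 12 months.

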### 3.2. Setting

The study is planned to span six years, including a recruitment period of 30 months followed by a 12-month follow-up period for each patient. Patients will be recruited from both outpatient consultations and hospital admissions.

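### Accuracy at 3, 17 and 38 months uses methods that need every patient's vital status at each horizon and is not linked to the planned Kaplan-Meier curves

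*Protocol article*

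**What the plan says.** Predicting mortality is the second primary objective (2.1), and its accuracy at 3, 17 and 38 months is a principal outcome (3.5). For the association of NECPAL status with "mortality at 3, 17, and 38 months, we will analyze sensitivity, specificity", PPV and NPV are the stated measures (5.2). The section continues: "Mortality rates will be compared using the chi-square test for equality of proportions".

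The same paragraph plans survival methods: "The Kaplan–Meier method will be used to estimate non-parametric survival curves, and the log-rank test will be applied to assess their differences", and "a semi-parametric Cox proportional hazards regression model will be performed to predict the risk of death". Neither sentence says that these estimates feed into the accuracy measures.

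On ascertainment, section 4 states: "Mortality data are collected through telephone follow-ups and chart reviews". The date of death is recorded. Section 3.3.2 excludes patients likely to be transferred or to leave the area. Section 5.1 states: "We applied a 10% oversampling rate to account for potential non-responses". No rate of loss to follow-up appears anywhere.

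**The concern.** A 2x2 table at month 38 has a cell for each patient only if that patient is a known death or was followed to month 38. A patient last reached alive at month 20 fits neither column. Two simple ways to force such patients into the table both bias it, even when loss is unrelated to prognosis:

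- **Dropping them.** Deaths before loss are kept and patients lost alive are removed, so mortality is overstated.
- **Counting them as alive.** Deaths after loss are missed, so mortality is understated.

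PPV is the mortality of the NECPAL+ group and NPV is the survival of the NECPAL- group, so both inherit the error directly. Sensitivity and specificity are also affected when loss differs between groups. The published PPV could then disagree with the study's own Kaplan-Meier curve at the same month.

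**Working it through.** **The plan's own figure.** 1.96² × 0.5 × 0.5 / 0.05² = 384.2, and 384 × 1.10 = 422.4, so 384 and about 420 reproduce. The 10% inflates a single-proportion precision calculation for non-response. It is not a loss rate.

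**Calendar.** Thirty months of recruitment from 1 February 2024 (3.1, 3.2) ends about 1 August 2026. Adding 38 months gives about 1 October 2029, before the stated completion date of 1 May 2030. The calendar alone censors nobody before month 38, so only loss to follow-up matters here.

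**Assumptions (not in the article).** 38-month mortality is 60% in NECPAL+ and 25% in NECPAL-. Half the cohort is NECPAL+. Death and loss times are exponential and independent. L is the probability of loss by month 38 in the absence of death, equal in both groups.

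**Formulas.** With mortality m, h = -ln(1 - m)/38 and c = -ln(1 - L)/38.

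- Observed deaths: D = h/(h + c) × [1 - (1 - m)(1 - L)]
- Known alive at month 38: A = (1 - m)(1 - L)
- Apparent mortality if lost patients are dropped: D/(D + A)
- Apparent mortality if they are counted as alive: D

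**Example, NECPAL+, L = 10%.** h = 0.02411 and c = 0.00277. D = 0.897 × (1 - 0.40 × 0.90) = 0.574 and A = 0.360. The PPV reads 0.574/0.934 = 61.5% or 57.4%, against a true 60.0%. Status is unknown for 1 - 0.574 - 0.360 = 6.6% of the group.

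| L | D, A (NECPAL+) | D, A (NECPAL-) | PPV % dropped / alive | NPV % dropped / alive | Risk difference, points, dropped / alive |
|---|---|---|---|---|---|
| 0 | 0.600, 0.400 | 0.250, 0.750 | 60.0 | 75.0 | 35.0 |
| 5% | 0.587, 0.380 | 0.244, 0.713 | 60.7 / 58.7 | 74.5 / 75.6 | 35.2 / 34.3 |
| 10% | 0.574, 0.360 | 0.238, 0.675 | 61.5 / 57.4 | 73.9 / 76.2 | 35.4 / 33.6 |
| 20% | 0.547, 0.320 | 0.225, 0.600 | 63.1 / 54.7 | 72.7 / 77.5 | 35.8 / 32.2 |

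**Unequal loss** (20% in NECPAL+, 10% in NECPAL-). Specificity is A-/(A- + A+) when lost patients are dropped: 0.675/(0.675 + 0.320) = 67.8%. Counted as alive it is (1 - 0.238)/[(1 - 0.238) + (1 - 0.547)] = 62.7%. The true value is 0.75/(0.75 + 0.40) = 65.2%.

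**Second scenario.** Take 60% NECPAL+ with stages I/II/III in the ratio 40/40/20, the article's 38, 17.2 and 3.6 months read as medians, and NECPAL- mortality of 20%. At 10% loss, a true PPV of 71.3% reads 72.8% or 68.9%, and a true NPV of 80.0% reads 79.1% or 81.0%. The risk difference of 51.3 points reads 51.9 or 49.9. Directions are the same and sizes similar.

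**Kaplan-Meier alternative.** Under independent censoring within group it estimates S+(38) = 0.40 and S-(38) = 0.75 consistently, so PPV = 60% and NPV = 75% at every L in the table. With complete follow-up it equals the 2x2 result exactly.

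**The case against.** The strongest reply is that section 5.2 is one paragraph of a journal article. It does not say that lost patients are dropped or counted as alive, and a handling rule may sit in a full protocol or analysis plan that is not shown. That stands: a reader might infer that the plan has chosen a biased rule, and it has not. What remains is that the methods actually named are ones that need complete status, while the survival methods named beside them are left unconnected.

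A reader might also infer that the whole mortality comparison is unsound. The article does not support this. Log-rank and Cox analyses are planned alongside the chi-square test, and with equal 10% loss the complete-case risk difference moves by only 0.4 points.

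Nor can the 10% in section 5.1 be read as expected loss over 38 months. It is labelled non-response. The exclusion of patients likely to move, and the use of chart review as well as telephone calls, should keep losses down.

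Finally, the shifts are modest against sampling error. With 210 NECPAL+ patients the 95% half-width for a PPV of 60% is 1.96 × √(0.6 × 0.4/210) = 6.6 points, larger than any single shift in the table. That is fair, but bias adds to sampling error and the interval would not show it. At 20% loss the choice of handling alone separates the two PPVs by 63.1 - 54.7 = 8.4 points.

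**Conclusion.** The point holds as a weakness in a stated method for a principal outcome, of moderate and conditional size. Under the assumed mortalities and independent, equal loss of 5% to 20%:

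- PPV is overstated by 0.7 to 3.1 points (dropped) or understated by 1.3 to 5.3 points (counted as alive).
- NPV moves by 0.5 to 2.5 points in one direction or the other.
- The risk difference moves by less than 1 point (dropped) or falls by up to 2.8 points (counted as alive).

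The directions follow from the structure of the table. The sizes rest on assumed mortality, prevalence and loss, none of which the article gives. If losses prove negligible, so does the bias.

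A reader might add the much larger distortion that would follow if follow-up really stopped at 12 months, since section 3.2 describes recruitment "followed by a 12-month follow-up period for each patient". That is a contradiction with the 17- and 38-month endpoints in sections 3.1, 3.5, 3.7.1, 4 and 5.2, and the passages must be reconciled. It is not evidence of loss to follow-up. A Kaplan-Meier curve ending at 12 months could not supply S(38) either.

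**What to change.** In section 5.2, estimate accuracy at each horizon t from the planned Kaplan-Meier curves by NECPAL group, with p the proportion NECPAL+:

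- PPV(t) = 1 - S+(t)
- NPV(t) = S-(t)
- Sensitivity(t) = p[1 - S+(t)] / {p[1 - S+(t)] + (1 - p)[1 - S-(t)]}
- Specificity(t) = (1 - p)S-(t) / {pS+(t) + (1 - p)S-(t)}

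Give bootstrap confidence intervals. Compare mortality at t by the difference in Kaplan-Meier estimates with a Greenwood standard error, in place of the chi-square test. Keep the 2x2 tables, among patients of known status, as a sensitivity analysis.

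Three additions make this work. Record the last-known-alive date in the eCRF, since section 4 mentions only the date of death. Report the number with unknown status in each NECPAL group at each horizon. State that the estimates assume censoring independent of prognosis within NECPAL group; if sicker patients are harder to reach, Kaplan-Meier is biased too.

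The cost is one extra date field, a short bootstrap routine and slightly wider intervals. The article reports 105 patients included at the time of writing (3.4), so the date can be collected for most of the cohort from entry.
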